## Abstract

**Background:**

Intraoperative hemodynamic management is intended to ensure adequate tissue perfusion and oxygen delivery and eventually help avoid organ injury. However, the optimal strategy for intraoperative hemodynamic management in patients having non-cardiac surgery remains unclear. We here report the protocol of a trial designed to test the hypothesis that personalized intraoperative hemodynamic management targeting preoperative baseline cardiac index reduces the incidence of a composite outcome of major postoperative complications and death within 7 days after surgery compared to routine hemodynamic management in high-risk patients having elective major abdominal surgery.

**Methods:**

The PELICAN trial is an international multicenter randomized trial in 1,128 high-risk patients having elective major abdominal surgery. The individual preoperative baseline cardiac index is determined with the patient being awake and resting in the supine position using noninvasive bioreactance. Patients are randomized to personalized hemodynamic management (intervention) or to routine hemodynamic management (control) during surgery. In patients assigned to personalized hemodynamic management, intraoperative cardiac index is maintained at least at the preoperative baseline cardiac index. In patients assigned to routine hemodynamic management, it is performed as per anesthesiologist preference (with blinded cardiac index monitoring). The primary outcome is the incidence of a composite outcome (“any event versus none”) of acute kidney injury, acute myocardial injury (including myocardial infarction), non-fatal cardiac arrest, severe infectious complications, and death within 7 days after surgery.

**Discussion:**

Our trial will determine whether personalized intraoperative hemodynamic management targeting preoperative baseline cardiac index reduces the incidence of major postoperative complications and death within 7 days in high-risk patients having elective major abdominal surgery compared to routine hemodynamic management.

**Trial registration:**

ClinicalTrials.gov Identifier NCT05648279. Registered on 5 December 2022.

**Supplementary Information:**

The online version contains supplementary material available at 10.1186/s13063-026-09657-9.

## Background

Intraoperative hemodynamic management is intended to ensure adequate tissue perfusion and oxygen delivery and eventually help avoid organ injury [1, 2]. However, the optimal strategy for intraoperative hemodynamic management in patients having non-cardiac surgery remains unclear [3–5]. Many protocols for intraoperative hemodynamic management focus on maximizing stroke volume or cardiac index during surgery. However, two recent multicenter trials reported that this approach did not improve patient-centered outcomes [6, 7].

In contrast, we consider the theory that intraoperative cardiac index targets should be personalized for each patient based on their individual preoperative baseline cardiac index. Our theory is supported by a single-center pilot trial [8] in which personalized intraoperative hemodynamic management targeting preoperative baseline cardiac index – compared to routine care – reduced a composite outcome of major postoperative complications and death within 30 days after surgery in high-risk patients having elective major abdominal surgery.

We here report the protocol of a trial designed to test the hypothesis that personalized intraoperative hemodynamic management targeting preoperative baseline cardiac index reduces the incidence of a composite outcome of acute kidney injury, acute myocardial injury, non-fatal cardiac arrest, severe infectious complications, and death within 7 days after surgery compared to routine hemodynamic management in high-risk patients having elective major abdominal surgery.

## Methods/design

### Trial design and setting

The “Personalized hemodynamic management targeting preoperative baseline cardiac index in high-risk patients having major abdominal surgery” (PELICAN) trial is an international multicenter randomized controlled single-blind clinical trial in high-risk patients having elective major abdominal surgery. The coordinating center for this trial is the University Medical Center Hamburg-Eppendorf, Hamburg, Germany. We plan to enroll 1,128 patients in 12 university medical centers (6 centers in Germany, 3 centers in Denmark, 1 center in Austria, 1 center in the Czech Republic, and 1 center in Spain). The trial is being conducted in agreement with the Declaration of Helsinki [9] and the ICH E6 R2 guidelines. The primary ethics committee for this trial is the ethics committee Hamburg (Ethikkommission der Ärztekammer Hamburg, Hamburg, Germany) which approved the trial on 15 December 2022 (registration number 2022–100955-BO-ff). Secondary approvals are obtained for each trial site by their respective ethics committee before patient recruitment starts. Written informed consent is being obtained from all participating patients. The trial was registered at ClinicalTrials.gov (NCT05648279) on 5 December 2022. We present the trial protocol following the Standard Protocol Items: Recommendations for Interventional Trials (SPIRIT) statement (Additional File 1) [10].

### Patients

Patients ≥ 45 years old who are scheduled for elective major abdominal surgery (involving visceral organs) under general anesthesia with an expected duration of surgery of ≥ 90 min AND who have at least one high-risk criterion are eligible for inclusion in the trial. The high-risk criteria are: exercise tolerance < 4 metabolic equivalents as defined by the guidelines of the American College of Cardiology/American Heart Association; renal impairment (serum creatinine ≥ 1.3 mg/dL or estimated glomerular filtration rate < 90 mL/min/1.73m^2^ within the last 6 months; coronary artery disease; chronic heart failure (New York Heart Association Functional Classification ≥ II); valvular heart disease (moderate or severe); history of stroke; peripheral arterial occlusive disease (any stage); chronic obstructive pulmonary disease (any stage) or pulmonary fibrosis (any stage); diabetes mellitus requiring oral hypoglycemic agent or insulin; immunodeficiency due to a disease (e.g., HIV, leukemia, multiple myeloma) or therapy (e.g., immunosuppressants, chemotherapy, radiation, steroids [above Cushing threshold]); liver cirrhosis (any Child–Pugh class); body mass index ≥ 30 kg/m^2^; history of smoking within two years of surgery; age ≥ 65 years; expected surgery duration ≥ 180 min; or B-type natriuretic peptide > 80 ng/L or N-terminal B-type natriuretic peptide > 200 ng/L within the last 6 months.

We do not include patients having ambulatory surgery, nephrectomy, liver or kidney transplantation surgery, or emergency surgery. We also do not include patients who had kidney, liver, heart, or lung transplantation; who have sepsis (according to current Sepsis-3 definition); who are classified American Society of Anesthesiologists physical status V or VI; who are pregnant; in whom it is impossible to perform cardiac index monitoring using the Starling Fluid Management System (Baxter, Deerfield, IL, USA); or who are participating in another clinical trial or treatment with a similar biological mechanism or primary outcome measure.

### Protocol

Figure 1 and Table 1 summarize and illustrate key aspects of the trial. Individual preoperative baseline cardiac index is determined with the patient being awake and resting in the supine position using the noninvasive bioreactance Starling Fluid Management System (usually at least one day before surgery). The individual preoperative baseline cardiac index is defined as the average value over a period of 5 min.

**Fig. 1 Fig1:**
[figure not shown]
Flowchart illustrating patient screening, enrollment, randomization, trial intervention, and outcomes. Patients meeting eligibility criteria undergo preoperative baseline cardiac index measurement, followed by 1:1 randomization to either personalized hemodynamic management (intervention) or routine hemodynamic management (control). The intervention is applied intraoperatively (from start to end of surgery). The primary outcome is assessed on postoperative day 7

**Table 1 Tab1:** Frequency and scope of trial visits

**Day**	**preoperative**	**perioperative**	**postoperative**						
	**-x to 0**	**0**	**1**	**2**	**3**	**4–6**	**7**	**30**	**90**
**Visits/contacts**	**I**	**II**	**III**	**IV**	**V**	**VI**	**VII**	**VIII**	**IX**
Informed consent	X								
Baseline assessment (i.e., demographic data, medical history)	X								
Preoperative baseline cardiac index measurement	X								
Blood sampling #1 (baseline values)	(X)	X							
Randomization		X							
Intraoperative cardiac index management		X							
Blood sampling #2, 3, 4, and 5			X	X	X	(X)	X*		
Primary outcome assessment							X		
Secondary outcome assessments					X		X	X	X
Serious adverse event documentation		X	X	X	X	X	X	X	X

^*^If the patient is discharged earlier than day 7, creatinine and high-sensitivity troponin concentrations will be required on the day of hospital discharge

Patients are randomized in a 1:1 ratio using central block-wise randomization with variable block length to personalized hemodynamic management (intervention) or to routine hemodynamic management (control). Randomization is stratified by center and is performed using an online system, usually on the day of surgery shortly before the start of induction of general anesthesia.

In patients assigned to personalized hemodynamic management, clinicians are instructed to maintain intraoperative cardiac index at least at the preoperative baseline cardiac index. In patients with a preoperative baseline cardiac index lower than 2.2 L/min/m^2^, the intraoperative cardiac index target is defined as ≥ 2.2 L/min/m^2^. Intraoperative cardiac index is measured using the Starling Fluid Management System. Patients assigned to personalized hemodynamic management receive balanced crystalloids at a baseline infusion rate of 6 mL/kg/h and additional 500 mL fluid boluses and dobutamine according to a treatment algorithm (Fig. 2). Mean arterial pressure is maintained above 65 mmHg. The trial intervention starts at the beginning of surgery and ends at the end of surgery.

**Fig. 2 Fig2:**
[figure not shown]
Treatment algorithm for patients assigned to personalized hemodynamic management

In patients assigned to routine hemodynamic management, hemodynamic management is performed as per anesthesiologist preference. Intraoperative cardiac index is measured using the Starling Fluid Management System, but the clinicians are blinded to cardiac index measurements. Cardiac index monitoring can be unblinded upon request. Mean arterial pressure is maintained above 65 mmHg.

### Outcomes

The primary outcome is the incidence of a composite outcome (“any event versus none”) of acute kidney injury, acute myocardial injury (including myocardial infarction), non-fatal cardiac arrest, severe infectious complications, and death within 7 days after surgery. We will assess the following secondary outcomes:Incidence of the composite primary outcome within 3 days after surgeryIncidences of each of the individual components of the primary outcome within 3 and 7 days after surgeryIndividual incidences of fever, respiratory infection, neurological infection, urinary system infection, colitis or infection with Clostridium difficile, endometritis, surgical site infection, deep incisional surgical site infection, organ or space surgical site infection (including anastomotic leakage), unknown infection with pathogenic organisms in tissue or fluid, and sepsis within 7 days after surgeryCollapsed incidence and individual incidences of need for renal replacement therapy, myocardial infarction, non-fatal cardiac arrest, and death within 30 days and 90 days after surgeryTime to transfer from intensive care unit to normal ward within 90 days after surgeryTime to hospital discharge within 90 days after surgeryIncidence of unplanned hospital re-admission within 30 days after surgery

Acute kidney injury will be defined as an increase in serum creatinine of ≥ 50% from baseline or need for renal replacement therapy [11]. Acute myocardial injury will be defined as an increase in high-sensitivity troponin according to the definition of “myocardial injury and infarction associated with non-cardiac procedures” set forth in the Fourth Universal Definition of Myocardial Infarction (2018) [12]. Serum creatinine and high-sensitivity troponin I or T (depending on the used assay in each center) will be measured before surgery (baseline; within 30 days before surgery) and on postoperative days 1, 2, 3, and 7. When patients are discharged earlier, serum creatinine and high-sensitivity troponin will be measured on the day of hospital discharge.

Severe infectious complications will be defined according to the “Standardised Endpoints in Perioperative Medicine” initiative [13] and include fever, respiratory infection, neurological infection, urinary system infection, colitis or infection with *Clostridium difficile*, endometritis, surgical site infection, deep incisional surgical site infection, organ or space surgical site infection (including anastomotic leakage), unknown infection with pathogenic organisms in tissue or fluid, and sepsis. 

Non-fatal cardiac arrest will be defined as successful resuscitation from either documented or presumed ventricular fibrillation, sustained ventricular tachycardia, asystole, or pulseless electrical activity requiring cardiopulmonary resuscitation, pharmacological therapy, or cardiac defibrillation. Death will be defined as all-cause mortality.

Data for the outcome assessment will be collected using medical records and telephone interviews on postoperative days 3, 7, 30 and 90. Serious adverse events will be documented during the trial.

### Sample size

The sample size calculation is based on the composite primary outcome. The incidence of the primary outcome was estimated to be 45% in the routine hemodynamic management group and 35% in the personalized hemodynamic management group. These estimates were based on our own pilot trial [8], which reported a 30-day composite outcome incidence of 41% in the routine care group; the OPTIMISE trial [14], which reported major complication rates of approximately 43% in control patients having major gastrointestinal surgery, and the OPTIMISE II trial protocol [15], which anticipated composite outcome rates of 45–50% in high-risk surgical patients. Our estimated 45% baseline rate is conservative and consistent with this body of evidence for high-risk patients with similar inclusion criteria. The assumed absolute risk reduction of 10% is based on an own pilot trial that investigated the effect of personalized intraoperative hemodynamic management targeting preoperative baseline cardiac index compared to routine hemodynamic management on postoperative complications and death [8].

We use a group-sequential design with one unblinded interim analysis (unblinded to an independent statistician and the members of the Data and Safety Monitoring Board (DSMB)) using the O’Brien-Fleming spending function [16]. A total sample size of 1014 patients, i.e., 507 patients per group, is required to achieve 90% power in the detection of a difference of 10% between the group incidences at a global significance level of 5% using a two-sided test of proportions without continuity correction including an unblinded interim analysis after 50% of patients are recruited. Allowing a total drop-out rate of 10% (assuming an 8% drop-out rate before randomization and 2% after randomization), a total sample size of 1,128 patients, i.e., 564 patients per group, is to be recruited. It is assumed that all patients stay within their treatment group. PASS version 2008 was used for the sample size calculation.

### Statistical analyses

Descriptive analyses will be performed to describe the patient characteristics and clinical data. The primary and secondary outcomes will be analyzed in the modified intention-to-treat population. The modified intention-to-treat population includes all patients who consented, were randomized, and had surgery. The final primary outcome analyses will be conducted using a two-sided test of proportions without continuity correction.

After a total of 564 patients had been observed for 7 days, an unblinded interim analysis was performed according to a pre-specified statistical analysis plan. It was conducted using a one-sided test of proportions without continuity correction. If the resulting p-value would have been < 0.0015 one-sided, the null hypothesis would have been rejected, and the trial would have been stopped for efficacy. However, recruitment continues. At the end of the trial, the statistical test for the primary outcome will be performed at a significance level of 0.049 two-sided.

In secondary outcome analyses, the incidences of each of the individual components of the primary outcome and the incidences of the additional secondary outcomes will be analyzed using a two-sided test of proportions without continuity correction. All time-to-event outcomes will be, due to the competing event death, assessed using Aalen-Johansen estimators and accompanied by effect estimates based on cause-specific Cox regressions.

In further analyses, the primary and secondary outcome analyses will be repeated in the per protocol population. As a sensitivity analysis, the primary outcome will be analyzed using a mixed effects logistic regression model including a fixed effect for the randomized treatment group and a random intercept for center to account for the cluster structure in the data. 

A full statistical analysis plan will be developed before any data is evaluated. Reporting will be consistent with Consolidated Standards of Reporting Trials guidelines [17]. Statistical analyses will be performed with standard statistical software such as SAS or R.

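### Randomization is stratified by center but the confirmatory test leaves center out: valid and adequately powered, but mildly conservative if event rates differ between centers

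*Protocol article*

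**What the plan says.** The randomization paragraph of the article's Protocol subsection describes 1:1 blocked allocation ("Patients are randomized in a 1:1 ratio using central block-wise randomization with variable block length") and names the stratification factor: "Randomization is stratified by center and is performed using an online system". Trial design and setting gives the number of strata: "We plan to enroll 1,128 patients in 12 university medical centers", spread over five countries.

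Statistical analyses then fixes the confirmatory test: "The final primary outcome analyses will be conducted using a two-sided test of proportions without continuity correction", at a final two-sided level of 0.049. No center term is mentioned and no reason is given for leaving it out. The same section does bring center in, but in a secondary role: "As a sensitivity analysis, the primary outcome will be analyzed using a mixed effects logistic regression model", with "a random intercept for center to account for the cluster structure in the data".

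Sample size uses the same unadjusted test, with event rates "estimated to be 45% in the routine hemodynamic management group and 35% in the personalized hemodynamic management group". It arrives at 507 evaluable patients per group for 90% power and 564 per group recruited.

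**The concern.** Blocking within center balances the arms inside each center, so differences between centers largely cancel out of the treatment contrast. The crude standard error does not reflect this: it treats all patients in an arm as draws from one common risk and counts between-center variation as noise. The test statistic is then slightly too small on average, and the true type I error lies below the nominal level.

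The article itself gives grounds to expect some variation between centers. One component of the composite is defined by "high-sensitivity troponin I or T (depending on the used assay in each center". Infections, another component, are ascertained from medical records and telephone interviews in five countries. The plan acknowledges the center structure but leaves it out of the test that decides the trial.

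At stake is a little efficiency and the match between design and analysis. The validity of the result is not threatened.

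**Working it through.** **1. The plan's own figures.** With rates 0.45 and 0.35, mean 0.40, z = 1.9686 for two-sided 0.049 and 1.2816 for 90% power:

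n per group = (1.9686·√(2·0.40·0.60) + 1.2816·√(0.45·0.55 + 0.35·0.65))² / 0.10² = (1.3639 + 0.8833)² / 0.01 ≈ 505.

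At 507 per group the power is 90.1%. O'Brien-Fleming-type spending at half information gives 0.0015 one-sided at the interim and 0.0490 two-sided at the end; power with the interim included is 90.1% to 90.3%. For drop-out, 507/0.90 = 563.3, hence 564 per group and 1,128 in total. All stated figures reproduce, and they belong to the same crude test that the analysis section uses.

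**2. Effect of leaving center out.** Let ICC be the share of outcome variance that lies between centers. With arms balanced within centers, the true variance of the difference is about (1 − ICC) times the variance that the crude test uses. Write v = √(1 − ICC), SE0 = √(2·0.24/507) = 0.03077 and SE1 = √(0.475/507) = 0.03061. Then:

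- Crude type I error = 2·[1 − Φ(1.9686/v)]
- Crude power = Φ((0.10 − 1.9686·SE0)/(v·SE1))
- Stratified power = Φ((0.10 − 1.9686·v·SE0)/(v·SE1))

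At ICC 0.10, v = 0.9487. Type I error is 2·[1 − Φ(2.075)] = 3.8%. Crude power is Φ(0.03943/0.02904) = Φ(1.358) = 91.3%. Stratified power is Φ(0.04254/0.02904) = Φ(1.465) = 92.9%.

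**3. Simulation.** Setup: 1,014 patients, 12 centers, near-balanced arms within center, logit-normal center risks, one final look at 0.049, and a Cochran-Mantel-Haenszel (CMH) test without continuity correction as the stratified alternative. The ICC is assumed; the article gives none.

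| Assumed ICC | Type I error, crude | Power, crude | Power, CMH | Gain (points) |
|---|---|---|---|---|
| 0 | 4.8% | 90.0% | 89.9% | about 0 |
| 0.02 | 4.5–4.7% | 90.5% | 90.8% | about 0.3 |
| 0.055 | 4.3% | 90.8% | 91.6% | about 0.8 |
| 0.10 | 3.8–3.9% | 91.1% | 92.6–92.7% | about 1.5 |

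The type I error of the CMH test stays at about 4.8–5.0% throughout. Strongly unequal center sizes give similar results. In patients, the stratified test needs roughly (1 − ICC)·1,014: 994 at ICC 0.02, 963 at 0.05 and 913 at 0.10.

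**4. What these ICCs imply.** For a marginal control rate of 45%, the central 95% of center-specific rates is expit(m ± 1.96·SD) on the logit scale:

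- ICC 0.02 (SD 0.29, m ≈ −0.20): about 32% to 59%
- ICC 0.055 (SD 0.5, m ≈ −0.21): about 23% to 68%
- ICC 0.10 (SD 0.7, m ≈ −0.22): about 17% to 76%

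The last line describes very large differences between centers.

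**5. Crude interim, stratified final.** Under the null hypothesis the crude interim statistic has variance 1 − ICC, the stratified final statistic has variance 1, and their correlation is √0.5. Overall two-sided error = 2·[1 − P(Z1 ≤ 2.968/v, Z2 ≤ 1.9686)], where 2.968 is the normal quantile for 0.0015 one-sided. This gives 0.0500 at ICC 0, 0.0497 at 0.055 and 0.0495 at 0.10. Changing the final test does not break the alpha already allocated.

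**The case against.** The strongest reply is that nothing in the plan is wrong. The trial was sized for the crude test and is analyzed with it, planned power is met in every scenario, and the error is on the safe side. A center-adjusted model is already prespecified, so readers will see whether adjustment changes the result. All sites are large university hospitals with common eligibility criteria and outcome definitions, so a small ICC is plausible, and at 0.02 the gain is about 0.3 points. The interim has also been done with the crude test, so changing the final test is more than an editorial step.

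Most of this stands, and it sets the size of the point. Two things remain. The mixed model does not carry the confirmatory conclusion, and it estimates a conditional odds ratio, whereas the trial is planned on a 10-point risk difference. And the interim calls for care but does not block the change: it was unblinded only to an independent statistician and the monitoring board, and overall alpha holds.

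A reader might infer more than the article supports:

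- **That the type I error is inflated.** The direction is the opposite.
- **That the trial is underpowered or gives away planned power.** Crude power stays at about 90% or more; the loss is only relative to a somewhat better test.
- **That the test is seriously conservative.** This would need strong center differences, for which the article offers no figure.
- **That the reported confidence interval will be too wide.** The article names no interval method for the primary outcome, so this cannot be shown.

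**Conclusion.** The point holds as a minor mismatch between design and confirmatory analysis. It concerns efficiency only. Over the assumed ICC range of 0 to 0.10, leaving center out costs between nothing and about 1.5 points of power relative to a stratified test, and under 1 point up to ICC 0.055. The actual type I error lies between roughly the nominal 4.9% and 3.8–3.9%.

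These figures rest on the planned event rates, 1,014 evaluable patients in 12 centers, near-balance within centers and logit-normal center effects. The direction is certain whenever center rates differ. The size is uncertain, because it depends on an ICC that the article does not give.

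**What to change.** Make the final primary test a Cochran-Mantel-Haenszel test stratified by center, without continuity correction, at two-sided 0.049. Report a Mantel-Haenszel risk difference with its confidence interval, which keeps the planned effect scale. Retain the crude test of proportions and the mixed logistic model as sensitivity analyses. Carrying the stratification over to secondary binary outcomes and the Cox models is optional.

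No new data are needed, but the cost is more than one edited sentence. Because the interim used the crude test, the change needs a dated protocol and SAP amendment, written by staff without knowledge of the interim results and completed before unblinding, with a record of both. Methods against bias says the analysts stay blinded until the final analysis, so this is possible in principle. Trials status expected recruitment to end in September 2025, so time may be short.

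If that window has closed, leave the crude test as primary, give the reason for omitting center, and report the center-stratified risk difference beside it.

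### Neither the primary test nor the sensitivity model uses a patient-level baseline covariate, so a modest and low-cost gain in power is left unused

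*Protocol article*

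**What the plan says.** The Statistical analyses section is explicit about the confirmatory method: "The final primary outcome analyses will be conducted using a two-sided test of proportions without continuity correction". The sample size rests on the same test, "at a global significance level of 5% using a two-sided test of proportions without continuity correction". The one regression planned for the primary outcome is a sensitivity analysis, a mixed logistic model "including a fixed effect for the randomized treatment group and a random intercept for center", whose stated purpose is to allow for clustering by center.

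The trial nonetheless gathers patient-level information before the intervention:

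- Table 1 schedules demographics, medical history and a cardiac index measurement before surgery. The Fig. 1 caption places the "preoperative baseline cardiac index measurement" ahead of randomization.
- The Outcomes section states that creatinine and high-sensitivity troponin "will be measured before surgery (baseline; within 30 days before surgery").
- Age, renal impairment, cardiac disease and expected duration of surgery are among the high-risk eligibility criteria in the Patients section, and one criterion is enough for entry.
- Randomization is stratified by center only (Protocol section).

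**The concern.** Two components of the composite are read from postoperative creatinine and troponin, and the protocol itself uses age, renal and cardiac status and length of surgery to define high risk. Because a single criterion suffices, baseline risk probably differs widely between patients. When such values predict the outcome, leaving them out keeps that variation in the error of the treatment comparison. Neither the stratification nor the analysis recovers it, and a center intercept carries only what differs between centers.

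The stake is efficiency. It would matter most if the true effect is smaller than planned. The 10-point reduction comes from the group's own single-center pilot trial, and the Discussion cites three multicenter trials of other cardiac output or stroke volume targets that showed no benefit.

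**Working it through.** **Inputs from the documents.** Event rates are "estimated to be 45% in the routine hemodynamic management group and 35% in the personalized hemodynamic management group". The size is 507 per group. There is one interim look at half the patients with O'Brien-Fleming spending, a one-sided interim limit of 0.0015 and a final two-sided level of 0.049.

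**Input not in the documents.** The share of outcome variance explained by baseline values, R², is assumed to be 5% to 12%. In simulation this corresponds to an AUC of roughly 0.63 to 0.70.

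**Step 1: the plan's own figures.** O'Brien-Fleming-type spending of 0.025 per side at half information gives an interim limit of 0.00153 one-sided (z = 2.963) and a final level of 0.0490 two-sided (z = 1.969). With pooled variance, 90% power needs 506.1, hence 507 per group. The stated size and both limits reproduce.

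**Step 2: unadjusted precision and power.**

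- SE = √[(0.45 × 0.55 + 0.35 × 0.65)/507] = √(0.475/507) = 0.0306.
- The 95% half-width is 1.96 × 0.0306 = 6.0 points.
- Looking at the final analysis alone, power ≈ Φ(0.10/0.0306 − 1.969) = Φ(1.298) ≈ 90.3%. The full two-look calculation also gives 90.3%.

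**Step 3: adjusted analysis.** For a standardized (marginal) risk difference, the variance is multiplied by about (1 − R²).

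| R² | SE | Fall in SE, 1 − √(1 − R²) | 95% half-width | Power, 45% vs 35% | Equivalent extra patients, 1,014/(1 − R²) − 1,014 |
|---|---|---|---|---|---|
| 0 | 0.0306 | 0 | 6.0 | 90.3% | 0 |
| 0.05 | 0.0298 | 2.5% | 5.8 | 91.7% | 53 |
| 0.10 | 0.0290 | 5.1% | 5.7 | 93.0% | 113 |
| 0.12 | 0.0287 | 6.2% | 5.6 | about 93.5% | 138 |

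**Step 4: smaller true effect.** At 45% vs 37%, power is 73.7% unadjusted, 75.8% at R² = 0.05 and 78.0% at R² = 0.10.

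**Step 5: simulation check** (507 per group, 3,000 runs per setting, level 0.049, standardized logistic risk difference with robust SE).

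- Power rose from 89.5% to 90.9% at R² = 0.056 and from 90.2% to 93.2% at R² = 0.123.
- With a covariate of no prognostic value, power was 90.2% adjusted and 90.3% unadjusted.
- Adjusted type I error was 4.8% to 5.2%. A second set of runs gave 4.9% to 5.6%. The Monte Carlo SE is √(0.05 × 0.95/3,000) = 0.4 points. This is close to nominal, with a hint of a slightly small robust SE at the upper end.

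**Step 6: crude interim followed by an adjusted final test.** The correlation between the looks falls from √0.5 = 0.707 to 0.707 × √(1 − R²), that is 0.689 at R² = 0.05 and 0.663 at R² = 0.12. With the one-sided interim limit and the two-sided final test at 0.049, overall error is about 0.0495 to 0.0496, provided the final test holds its level exactly.

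**The case against.** The strongest reply is that nothing here is wrong. The crude test is valid, needs no model and no rule for missing covariates, targets the marginal risk difference, and matches both the sample size basis and the interim analysis already done. It delivers its planned power. All of this stands. A reader might infer that the crude analysis gives up power for nothing in return, or that chance imbalance biases it. The documents support neither: simplicity and consistency with the interim are real benefits, and under randomization the test's error rate already allows for chance imbalance.

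The size of the gain is also open to doubt. No prognostic strength is stated. Severe infectious complications include fever and urinary infection, which creatinine, troponin or cardiac index may not predict, and kidney injury is defined relative to baseline creatinine. The gain is therefore conditional, and a fall in SE as large as 8% would need about 15% of variance explained (1 − 0.92² = 0.154), beyond the range assumed here.

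Timing counts as well. The unblinded interim has taken place, and the Trials status section expected recruitment to end in September 2025. This limits who may choose the covariates and makes the change an amendment, but does not rule it out.

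Finally, the analysis plan is not shown and may contain adjusted supportive analyses. Their absence from the article is not the point raised here. The point is that the primary test is stated as unadjusted.

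**Conclusion.** The point holds as a missed efficiency gain in a stated method. It is not an error in the plan, and the claim of 90% power is correct. If baseline values explain 5% to 12% of outcome variance, adjustment adds about 1 to 3 points of power at the planned effect, taking it from about 90% to about 92% to 93%. It lowers the SE by about 3% to 6%, worth about 55 to 140 patients on 1,014. If the values are not prognostic, essentially nothing is lost.

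These figures rest on the assumed R² and on reporting a standardized risk difference. The conditional odds ratio from a logistic model is a different estimand, and its SE does not shrink in this way.

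**What to change.** Before final unblinding, have staff without access to the interim results lock a short covariate list. A workable list is age, log baseline creatinine, log baseline high-sensitivity troponin relative to the assay's upper reference limit (centers use troponin I or T), preoperative cardiac index, and expected duration of at least 180 min. Lock a simple rule for missing baseline values at the same time.

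Pre-specify a logistic model with treatment and these terms that reports the standardized risk difference with a robust SE, preferably with a small-sample correction. Make it the primary analysis at the same 0.049 level, with the crude test as supportive.

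If the sponsor keeps the crude test as confirmatory because the interim used it, name the adjusted standardized risk difference as the pre-specified key supportive estimate. State that this leaves the power of the confirmatory test unchanged.

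The cost is a protocol and SAP amendment after the interim, the missing-covariate rule and a little programming. No new data or patients are needed.
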